##### Sample size formula

The total sample size is calculated by the following standard formula: [60]

Here z_a _= 1.96 and z_b _= 1.28, for 90% power at the two-sided 0.05 level, Δ is the relevant effect size, and σ is the relevant standard deviation (SD). The sample size is then multiplied by the Inflation Factor (IF) and divided by the expected response rate of 0.8.

##### Specification of the effect size

The effect of SHS can be expressed as the ratio of the hair nicotine or cotinine level between exposed and unexposed populations. We assume that the program will reduce this ratio by 25%, 33%, or 50%. We further assume that, due to leakage of the program to the control group, the ratio will be reduced in the control group by an amount equal to 10% of the reduction in the treated group (i.e. 2.5%, 3.3%, or 5%).

We perform the calculations on a logarithmic scale. Denote by R the reduction achieved by the program. The effect size (i.e. difference between treatment groups) on the logarithmic scale is then given by

For R = 0.25, 0.33, and 0.50, the corresponding Δ values are Δ = 0.26, 0.37, and 0.64.

##### Estimation of the Inflation Factor (IF)

The IF is determined by the intraclass correlation coefficient (ICC) and the number of children per clinic [61]. The formula is IF = (1+(m-1)ρ), where m is the average number of children per clinic and ρ is the ICC. As was done by the authors of a previous study, we assume ρ = 0.005. Our assumed clinic size is m = 30. Hence the IF is given by IF = 1+29*0.005 = 1.145.

##### Estimation of the standard deviation (SD)

###### Hair Nicotine

Our endpoint is log hair nicotine level. Al-Deleimy et al. [59] presented geometric means and associated confidence intervals for hair nicotine. These results were generated by computing arithmetic means and associated confidence intervals for log hair nicotine and then backtransforming to the original hair nicotine scale. From the results presented in the Al-Deleimy paper, we can derive the SD for log hair nicotine in the Al-Deleimy study.

Al-Deleimy et al. presented data for nonsmoking families, parents who smoked only outside the house, and parents who smoked inside the house as well as outside. Table 2 presents the published results and the corresponding SD's for log hair nicotine. Given the above results, we estimate the SD for log hair nicotine at σ = 1.00.

**Table 2 T2:** Hair Nicotine Results From Al-Deleimy et al

	Published N	Published Geometric Mean	Published Confidence Interval	SD for Log Hair Nicotine
No exposure	101	0.58	[0.49,0.68]	0.84
Smoke outside the house	69	2.63	[2.03,3.40]	1.09
Smoke inside the house	127	5.62	[4.60,6.86]	1.15

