### Population

The study will be conducted in Israel, where 20.9% of the adult population smokes [41]. While there are no nationally representative data on young child exposure to SHS, one study conducted in Haifa showed that an estimated 46% of infants less than one year old resided in homes with one or more smokers [42]. Forty percent of school-aged children in seventh through twelfth grade are exposed to SHS in their homes [43].

All Israeli citizens are covered by the National Health Insurance Law through one of four Health Maintenance Organizations (HMOs). Participants for in-depth interviews, focus groups, and the Pilot Study will be recruited through three clinics owned by Meuhedet, an HMO which serves a million individuals. The clinics are located in three different cities in Israel, all of which are located in the center of the country. Each of these clinics will give us a unique perspective on trying to control secondhand smoke exposure in different populations.

City X has a middle-income heterogeneous population, City Y has a primarily Ultra-Orthodox population, and City Z has a mixed-income heterogeneous population which includes a high percentage of immigrants from the former Soviet Union. Men from the former Soviet Union smoke more frequently than native-born Jewish Israelis [44]. The Ultra-Orthodox males have rates of smoking which are similar to other Jewish males, while the Ultra-Orthodox females have very low smoking rates. Consequently, in the City Y clinic, the emphasis will be on controlling exposure of children in a population where many fathers smoke but few mothers do, while in the other areas, the focus will be on households where either parent smokes or both parents smoke.

Potential participants coming for a visit to their Meuhedet clinic will be find posters and flyers advertising for participants in the project. In addition, they will be approached by the clinic staff (physicians, nurses, health promoters, or secretaries) and asked to agree to be contacted by project personnel for possible participation in the study. The eligibility criteria are as follows:

1. The child is a Meuhedet member, cared for in one of the participating clinics.

2. At least one parent is a current smoker.

3. The child is of the appropriate age (< 3 years of age).

4. The child has sufficient hair growth for hair samples.

5. The parents give consent for participation in the research.

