#### Sample size calculation for the Phase III trial

The final sample size calculations for the Phase III trial will be based on results from the Phase II pilot study. Preliminary calculations have been made on the basis of published data for hair cotinine, and hair nicotine [58,59]. These calculations are based on a power of 0.8 and a 2-sided alpha-level of 0.05. The published data we have used are population or sample level data on levels of hair cotinine in children exposed or not exposed to SHS, or on levels of hair nicotine in children whose parents smoke in the house, smoke only outside the house, or do not smoke at all. We made the following assumptions:

a. The aspirational goal is elimination of TSE among the children. However, our more realistic, operative goal, on which sample size calculations were performed, is a *reduction *in exposure. We define a detectable change of substantive importance as one which produces a change in exposure equivalent to one third the difference in measured hair values between children exposed and unexposed to tobacco smoke.

b. There will be some leakage of the intervention to the control group, as a direct result of the recruitment process. This is consistent with the improvements seen in twelve out of eighteen trials in the control groups, of studies included for review in the Cochrane systematic review [4]. We assume that this contamination will occur in 10% of the recruited children in the control group. This number is based on observed changes in a previous health intervention trial which was run by two of the authors of the present study [39]. Thus, the expected outcome in the control group is a weighted average of the values for exposed children (90%) and the expected change as a result of the intervention (10%).

c. An Inflation Factor (IF) is necessary to compute sample sizes due to the possibility that some of the variance is due to similarities within children attending the same clinic. The inflation factor we used is 1.145.

d. We further assume that 20% of the children recruited will be lost to follow-up.

Based on our tentative calculations, a total of eighteen clinics will be randomized equally to intervention and control groups. Thirty children will be recruited from each clinic. Five hundred and forty infants will be recruited to the study.

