##### Calculated Sample Size

Given the foregoing development, the calculated total sample sizes for log hair nicotine and log hair cotinine at the various levels of R are as follows (rounded up to the nearest 10) as seen in Table 3.

**Table 3 T3:** Calculated Total Sample Sizes

	Log Hair Nicotine	Log Hair Cotinine
R = 0.25	880	1,160

R = 0.33	450	600

R = 0.50	150	200

The calculated sample sizes are higher for log hair cotinine than for log hair nicotine. This is consistent with the claims that hair nicotine is more sensitive than hair cotinine.

Using R = 0.33 and taking log hair nicotine as the endpoint, we get a total sample size of 450 infants. Since the number of infants has to be an even multiple of the clinic size, which we are assuming is 30, we get a total sample size of 480. We increase this to 540 infants as a security measure against possible clinic dropout and the uncertainty in the estimates used. We thus set the tentative total sample size at 540 infants (9 clinics in each of the two arms, with 30 infants per clinic). The final choice of endpoint and sample size will be made on the basis of locally-collected data.

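### The SD of 1.00 for log hair nicotine is below both Table 2 rows that match the eligible smoking families, so the 90%-power sample size is understated and 540 gives about 85–88%, not about 95%

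*Protocol article*

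**What the plan says.** In the protocol article, under *Hair Nicotine*, Table 2 takes geometric means and confidence intervals from a published study and derives an SD of log hair nicotine for each of three groups: no exposure 0.84 (n = 101), smoke outside the house 1.09 (n = 69), smoke inside the house 1.15 (n = 127). The text then concludes: "Given the above results, we estimate the SD for log hair nicotine at σ = 1.00". It does not show how the three values became 1.00.

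The eligibility list under *Population* includes: "At least one parent is a current smoker".

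Two power levels are given. *Sample size calculation for the Phase III trial* says: "These calculations are based on a power of 0.8 and a 2-sided alpha-level of 0.05". *Sample size formula* uses a z-value of 1.28 "for 90% power at the two-sided 0.05 level".

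*Calculated Sample Size* reports 450 infants for nicotine at R = 0.33. It rounds this to 480 to fit clinics of 30, and raises it to 540 to guard against clinic dropout and uncertain estimates. It calls 540 tentative, pending local data. It also remarks: "The calculated sample sizes are higher for log hair cotinine than for log hair nicotine", and treats this as in line with claims that nicotine is the more sensitive marker.

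**The concern.** The SD that governs power is the SD among the children who can be enrolled. Children of non-smoking families cannot be enrolled, so the 0.84 row is not evidence about this trial. Both remaining rows lie above 1.00, and no averaging of them can give a value below 1.09. Even with the ineligible row kept in, the pooled value is 1.04.

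Required sample size grows with the square of the SD, so a value that is too low understates the requirement and overstates the power of 540. It also bears on the step from 480 to 540, which the plan presents as protection against other risks.

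**Working it through.** **Inputs, all from the protocol article.** z-values 1.96 and 1.28 (*Sample size formula*); inflation factor 1.145 (*Estimation of the Inflation Factor*); response rate 0.8; leakage such that "the ratio will be reduced in the control group by an amount equal to 10% of the reduction in the treated group"; and the effect sizes "For R = 0.25, 0.33, and 0.50, the corresponding Δ values are Δ = 0.26, 0.37, and 0.64" (*Specification of the effect size*).

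The displayed formulas are missing from the text available to me. I used the standard forms below, and they reproduce the plan's figures:

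- Δ = ln[(1 − 0.1R)/(1 − R)]; at R = 0.33, ln(0.967/0.67) = 0.3669
- Total N = 4σ²(1.96 + 1.28)²/Δ² × 1.145/0.8

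**Step 1: reproduce the plan.** With σ = 1.00 and R = 0.33, N = 446.4, which rounds up to the stated 450. R = 0.25 gives 873.1 (stated 880) and R = 0.50 gives 145.9 (stated 150). With σ = 1.15 the cotinine column follows: 1154.7, 590.4 and 192.9 (stated 1,160, 600 and 200). At 80% power (z = 0.8416) the R = 0.33 nicotine figure would be 333.8, so Table 3 was built on 90%.

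**Step 2: check the row SDs.** √n × ln(upper/lower)/(2 × 1.96) gives 0.840, 1.093 and 1.149, matching Table 2.

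**Step 3: SD for the eligible rows.**

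- Pooled within group: √[(68 × 1.09² + 126 × 1.15²)/194] = 1.129, or 1.13.
- With the difference between the two group means added, at the cited study's split (p = 127/196 = 0.648): √[1.129² + p(1 − p) × ln(5.62/2.63)²] = √(1.275 + 0.228 × 0.577) = 1.186, or about 1.19.
- For comparison, all three rows pooled: √[(100 × 0.84² + 68 × 1.09² + 126 × 1.15²)/294] = 1.04. Their simple mean is 1.03.

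**Step 4: requirement and power.** Power = Φ(Δ/(σ√(2/n)) − 1.96). The effective n per arm is total × 0.8/1.145/2, which is 188.6 at 540. R = 0.33 throughout; N is before rounding up.

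| σ | Basis | N for 90% | N for 80% | Power at 480 | Power at 540 |
|---|---|---|---|---|---|
| 1.00 | plan | 446 | 334 | 91.9% | 94.6% |
| 1.09 | smoke outside only | 530 | 397 | 86.9% | 90.5% |
| 1.13 | two rows pooled | 570 | 426 | 84.5% | 88.4% |
| 1.15 | smoke inside only | 590 | 441 | 83.2% | 87.3% |
| 1.19 | pooled plus mean difference | 632 | 473 | 80.6% | 85.0% |

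The largest σ at which 540 keeps 90% is √(540/446.4) = 1.10.

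**Step 5: nicotine against cotinine.** Both columns of Table 3 use the same Δ. Their ratio is therefore (1.15/1.00)² = 1.3225, and 590.4/446.4 = 1.3225. The gap comes only from the two assumed SDs.

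**The case against.** - **The size is provisional and has an allowance.** The plan says the final calculation will use pilot results, and the rise to 540 names uncertain estimates as well as clinic dropout. This stands and limits the weight of the point. But the allowance does not fully cover σ = 1.13, for which 90% power already needs about 570. Even at 1.09 the requirement is 530, which leaves less than one clinic for dropout.
- **Power of 0.8 is also stated.** Against that target 540 is enough by the plan's formula (426 to 473 needed). This stands. A reader might infer that 540 is inadequate; the document supports only a shortfall against the 90% on which Table 3 was built.
- **Baseline hair nicotine will be a covariate** (*Statistical analysis*), so a residual SD governs power. This stands, but the sizing takes no credit for it and gives no correlation. If the residual SD is σ√(1 − r²), bringing it down to 1.10 needs r = √(1 − (1.10/1.13)²) = 0.23, or √(1 − (1.10/1.19)²) = 0.38. These are assumptions. The covariate would also absorb part of the inside/outside difference, so 1.19 is an upper figure and not the established SD. Its 127:69 split need not hold in the Israeli clinics.
- **The cause is not shown.** A reader might infer that the unexposed row "No exposure 101 0.58 [0.49,0.68] 0.84" was averaged in. The document does not say so, and averaging all three rows gives 1.03 to 1.04, not 1.00.
- **Cotinine.** A reader might infer that nicotine's advantage vanishes, since σ = 1.15 gives both markers the same N. That is not like for like. The cotinine SD is drawn from exposed and unexposed children, with no group SDs visible. With all nicotine rows pooled, N is 446.4 × 1.04² = 483, still below 590.

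**Conclusion.** The point holds, with modest consequences. σ = 1.00 is too low for the enrolled population on the plan's own table, whatever its derivation. At R = 0.33 and 90% power, the nicotine requirement is about 570 (σ = 1.13) to 632 (σ = 1.19) instead of 450. The tentative 540 gives about 88% to 85% instead of about 95%, a shortfall of 1.6 to 5 points from 90%.

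This rests on the plan's Δ, inflation factor, response rate and normal-approximation formula, on the cited study's SDs carrying over, and on no credit for baseline adjustment. The upper figure also assumes the 127:69 split. If all families resembled the smoke-outside group, 540 would still reach 90.5%.

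**What to change.** 1. Base σ on smoking families only, or on a stated residual SD after baseline adjustment estimated from the pilot, and show the derivation.
2. Recompute the nicotine column of Table 3 with that value.
3. Reconcile the two power statements (0.8 and 90%), since they decide whether 540 falls short.
4. Restate the power of 540 as about 85–88% before baseline adjustment. Say that the allowance for clinic dropout and uncertain estimates is largely or wholly taken up by the SD.
5. Keep the remark on nicotine's sensitivity, but add that the gap in Table 3 comes solely from the assumed SDs of 1.00 and 1.15.

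The cost is a recalculation and a slightly less favourable stated power. No added enrolment follows if that power is accepted. Holding 90% without credit for baseline adjustment would take about 570 to 632 infants, which is 20 to 22 clinics of 30 with equal arms.

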###### Hair Cotinine

Florescu et al. [58] presented descriptive statistics for hair cotinine for various populations. We focus on the population of children, either exposed or unexposed to tobacco smoke.

Florescu et al. state on page 440 of their paper that hair cotinine did not follow a normal distribution, and they therefore presented geometric means and some other statistics of interest. We take log hair cotinine as our endpoint, and assume that it is normally distributed. From standard mathematical results for the lognormal distribution, we can use the results in the Florescu et al paper to calculate estimates of the mean and SD of log hair cotinine.

The estimated means for log hair cotinine are in close agreement with the reported geometric means for hair cotinine previously reported [exp(-1.59) = 0.20 vs. 0.19, exp(-0.84) = 0.42 vs. 0.48]. Based on the results, we estimate the SD for log hair cotinine at σ = 1.15.

##### Calculated Sample Size

Given the foregoing development, the calculated total sample sizes for log hair nicotine and log hair cotinine at the various levels of R are as follows (rounded up to the nearest 10) as seen in Table 3.

**Table 3 T3:** Calculated Total Sample Sizes

	Log Hair Nicotine	Log Hair Cotinine
R = 0.25	880	1,160

R = 0.33	450	600

R = 0.50	150	200

The calculated sample sizes are higher for log hair cotinine than for log hair nicotine. This is consistent with the claims that hair nicotine is more sensitive than hair cotinine.

Using R = 0.33 and taking log hair nicotine as the endpoint, we get a total sample size of 450 infants. Since the number of infants has to be an even multiple of the clinic size, which we are assuming is 30, we get a total sample size of 480. We increase this to 540 infants as a security measure against possible clinic dropout and the uncertainty in the estimates used. We thus set the tentative total sample size at 540 infants (9 clinics in each of the two arms, with 30 infants per clinic). The final choice of endpoint and sample size will be made on the basis of locally-collected data.

### Ethical approval and trial registration

Institutional Review Board approval has been obtained from the Ethics Committee of the Sackler Medical Faculty at Tel Aviv University. All participants will provide written informed consent. The trial is registered with the NIH trials registry database (ClinicalTrials.gov Identifier: NCT01335178).

## Discussion

This paper describes the planning process, a proposed program and its theoretical rationale, and an evaluation design of an innovative intervention to protect young children from tobacco smoke exposure. The primary challenges of this work are to (1) develop an effective theory-based intervention, and (2) to measure the effects with sufficient accuracy and precision to detect a true interventional effect.

Existing reviews of published reports show, overall, that the effects of similar interventions were either small or nonexistent [13,62-65]. This is consistent with many findings of health promoting community based interventions [66]. Findings could be due to one or a combination of three reasons: either the intervention programs tested were ineffective, the programs were effective but were not sufficiently well implemented, or the measurement of the results was not sufficiently accurate to detect the effects of the intervention.

Our developed program builds on recent ideas of others from the fields of parenting, health communication (new media and online/offline approach), smoking cessation (group therapy), and reduction of exposure (CEASE materials for involvement of physicians, biochemical feedback for internalization about personal exposure levels, [name] for education about TSE in cars with smokers, and possible use of NRT for maintaining smoke-free homes and cars). We avoid the common failure of using "one shot" or very short-term interventions, by using multiple group meetings augmented by a website. Our developmental plan ensures that the full trial will not go forward until we have evidence of feasibility and some indication that it is effective (albeit in an uncontrolled manner).

## Conclusions

In this article we present our rationale for and method of program development, proposed intervention plan, and evaluation plan. We describe a design that draws on social marketing and behavior-change approaches that is parent-focused and allows parents to join the program, even if they initially do not intend to quit smoking, and offers them a group support system that will address their concerns and needs. We identify important challenges faced by researchers interested in developing and evaluating interventions to reduce child exposure to tobacco smoke face, and offer specific strategies to address them. The proposed approach and its rationale can serve to contribute to building the science base for the development and testing of intervention approaches for health-promoting practices, and in particular the protection of children from tobacco smoke exposure.

## Abbreviations

ETS: Environmental Tobacco Smoke; HMO: Health Maintenance Organizations; ICC: Interclass correlation coefficient; IF: Inflation Factor; NIH: (United States) National Institute of Health; NRT: nicotine replacement therapy; SD: standard deviation; SHS: Secondhand smoke; SHSe: Secondhand smoke exposure; SMS: short message service; TSE: tobacco smoke exposure
